#### Drug Interactions

1. This drug is a CYP2C9 inhibitor. Caution must be taken when coadministering this drug with other drugs metabolised through CYP2C9.
2. Concomitant administration of fluconazole at 200 mg once daily resulted in a two-fold increase in celecoxib plasma concentration. This increase is due to the inhibition of celecoxib metabolism via P450 2C9 by fluconazole. This drug should be introduced at the lowest recommended dose in patients receiving fluconazole. Plasma concentration of this drug and Fluvastatin may increase when the two are used concomitantly. Combination of this drug with CYP2C9 inducers, such as rifampicin, carbamazepine, and barbiturates, may decrease the plasma concentration of this drug.
3. According to an in vitro study, celecoxib is an inhibitor of CYP2D6 and may interact with medicinal products which are metabolised by CYP2D6. When administered concomitantly, this drug may increase the plasma concentrations of CYP2D6 substratied, such as antidepressants (tricyclics and SSRIs), neuroleptics, anti-arrhythmic medicinal products, and dextromethorphan. Dose reduction of such drugs may be necessary when starting concomitant administration with celecoxib. Dose increase of such drugs may be necessary when stopping concomitant administration with celecoxib.
4. In vitro study showed that this drug partially inhibits metabolism mediated by CYP 2C19. Though clinical relevance of this finding is not known, drugs metabolized by CYP2C19 include diazepam, citalopram, and imipramine.
5. ACE inhibitors or angiotensin II receptor blockers: NSAIDs may reduce the effect of anti-hypertensive medicinal products including ACE-inhibitors and angiotensin II receptor antagonists. Therefore, concomitant administration of celecoxib with ACE inhibitor or angiotensin II receptor blocker should be conducted with such interactions in mind. In patients with renal impairment (e.g., dehydrated or elderly patients), concomitant administration of NSAID including this drug with ACE inhibitor or angiotensin II receptor blocker may generally increase the risk of reversible acute renal failure. Therefore, such combination must be given with care, especially in elderly patients. Adequate hydration and regular renal function monitoring must be provided after starting such combination therapy.
6. Diuretics: Clinical studies, as well as post-marketing observations, have shown that NSAIDs can reduce the natriuretic effect of furosemide and thiazides in some patients. This response has been attributed to inhibition of renal prostaglandin synthesis. Patients must be carefully monitored for signs of renal failure while on combination therapy with the above drugs and NSAID.
7. This drug can be used with low-dose aspirin (325 mg/day or less). However, concomitant administration of aspirin with this drug increases the rate of GI adverse events, including ulceration or other complications, compared to use of this drug alone Because of its lack of platelet effects, this drug is not a substitute for aspirin for cardiovascular prophylaxis
8. Lithium: NSAID can increase the plasma concentration of lithium and renal clearance of lithium by inhibiting prostaglandin synthesis in the kidneys. Therefore, patients on NSAID and lithium combination therapy must be monitored carefully for signs of lithium toxicity.
9. Methotrexate: NSAIDs may reduce the tubular excretion of methotrexate leading to increased fatal hematological toxicity of methotrexate. Therefore, this drug should not be co-administered with high-dose methotrexate used for cancer treatment (greater than 15 mg/week), and co-administration of this drug with low-dose methotrexate must be carefully considered. Co-administration of celecoxib with methotrexate (dose for rheumatoid arthritis treatment) in rheumatoid arthritis patient did not exert a significant effect. However, appropriate monitoring must be exercised for methotrexate-associated toxicity during co-administration.
10. Coumarin-type anticoagulant (e.g. warfarin): warfarin and NSAID can have a synergetic effect on gastrointestinal bleeding. Therefore, patients on both drugs concomitantly may be at an increased risk of gastrointestinal bleeding. In a study that evaluates the effect of this drug on anticoagulatory activity of warfarin by administering 2-5 mg of warfarin in health subjects, there was no effect on anticoagulatory activity as evaluated by prothrombin time. However, according to post-marketing survey, significant bleeding associated with increased prothrombin time that can potentially be fatal has been reported in patients who received concomitant therapy with warfarin and this drug, especially in the elderly.
11. Co-administration of NSAID with cyclosporin or tacrolimus may increase renal toxicity of cyclosporin or tacrolimus. Therefore, when co-administering the above drugs, renal function must be monitored.
12. Administration of this drug with high fat diet delayed maximum plasma concentration by 1-2 hours and increased AUC by 10-20%.
13. Co-administration of this drug with antacids containing aluminum or magnesium resulted in 37% decrease in maximum plasma concentration and 10% decrease in total absortion. Patient must be monitoring for signs of renal failure during co-administration.
14. This drug must not be co-administered with NSAIDs other than low-dose aspirin (325 mg/day or less), as this may increase the risk of adverse events.
15. Corticosteroids: there is an increased risk of gastrointestinal adverse events (e.g., ulcer, bleeding), expecially in elderly (65 years old or more).

#### Special Populations

1. Pregnancy and breastfeeding
   1. In rat models, this drug is not known to delay delivery. However, effect of this drug on labor and delivery is not known.
   2. In developmental study on rabbit embryo and fetus, oral administration of 150 mg/kg/day or more (Equivalent to two times the AUC0-24 in humans with 200 mg twice daily administration) was associated with rare increase in fetal deformities such as rib fusion and sternal segment fusion and interventricular septal defect. In one out of two developmental studies on rat embryo and fetus, oral administration of 30 mg/kg/day or more (Equivalent to six times the AUC0-24 in humans with 200 mg twice daily administration) was associated with volume dependent increase in fetal diaphragmatic hernia. Also, administration of 50 mg/kg/day or more in rats (Equivalent to six times the AUC0-24 in humans with 200 mg twice daily administration) has been shown to result in increased pre- and post-implantation loss and embryo-foetal lethality. This toxicity was not observed when pregnancy was initiated 2 weeks after drug discontinuation.
   3. There are no clinical data on ths administration of this drug in pregnant women. Animal studies (rabbit and rat) showed reproductive toxicity including deformities, but no potential risk in human pregnancy is known. As this drug, like other prostaglandin synthesis inhibitors, may cause uterine incompetence or early closure of fetal ductus arteriosus, this drug should not be administered to pregnant women or women capable of becoming pregnant. If pregnancy is confirmed during administration of this drug, this drug must be discontinued.
   4. Mechanism of action of NSAIDs may hinder or delay folicular rupture, which may cause reversible infertility in certain women. Therefore, discontinuation of NSAIDs including this drug must be considered in women who are reproductively challenged or undergoing infertility tests.
   5. Inhibition of prostaglandin synthesis may adversely affect the pregnancy and/or the embryo/foetal development. Data from epidemiological studies suggest an increased risk of miscarriage after use of a prostaglandin synthesis inhibitor in early pregnancy. In animals, administration of a prostaglandin synthesis inhibitor has been shown to result in increased implantation failure.
   6. This drug is excreted in human milk at similar concentration as plasma. According to limited data on 1 study subject, this drug may also be transferred to human breastmilk. Many drugs may be transferred to human breastmilk and possibly cause severe adverse events. Therefore, either breastfeeding or drug administration must be discontinued considering the importance of drug administration in pregnant women.
2. Pediatric population
   1. The safety and efficacy of VIMOVO in children aged 0 to 18 years has not been established.
3. Elderly
   1. Older people are at an increased risk of renal, hepatic, and cardiac impairment. Administration fo this drug to elderly require adequate observation.
   2. According to previous clinical studies, there was no significant difference in efficacy between elderly and younger subjects. Studies that compare renal function (GFR, BUN, creatinine) and platelet function (bleeding time, platelet aggregation) did now show a difference between elderly and younger subjects. However, similarly to other NSAIDs including selective COX-2 inhibitors, spontaneous post-marketing adverse events such as fatal gastrointestinal adverse events and acute renal failure have been reported more frequently in elderly subjects.
   3. Dose adjustment is generally not required in the elderly. However, this drug must be initiated at minimum dosage in patients under 50 kg.

## Packaging and labelling

The investigational product will be supplied by the sponsor and will be boxed. The investigational product must be managed at study sites by the clinical study pharmacist or other qualified personnel. The experimental drug, Naxozol (in tablet form), and the comparator, Celebrex (in capsule form), will both be packaged and supplied in a box.

The following information will be specified on one panel per box in black, according to the Enforcement Rule of Medicinal Product Safety, Article 69 (6):

- - An indication that the investigational product is “for use in the clinical study only”.
  - The designated identification code.
  - The product code or generic name of the main active ingredient.
  - The manufacture code and use-by or re-test date.
  - Storage instructions.
  - The business name and address of the approval authority for the study protocol.
  - An indication that the investigational product “cannot be used for purposes other than the clinical study”.

For primary labeling of the direct product container, only the following information will be specified due to limited space: an indication that the investigational product is only for use in the clinical study, the business name of the authority approving the study protocol, the subject registration number, the product code or generic name of the active ingredient, the re-test date, and the manufacture date.

## Supply, handling, and storage

#### Supply

The experimental drug and the comparator will be supplied by [name] (Severance Hospital, Department of Orthopedics).

#### Handling

Both the experimental drug and the comparator must be managed at the study sites by the clinical trial pharmacist or other qualified personnel.

#### Storage

The investigational products must be stored in sealed containers.

Use-by date:

- - - Experimental drug: written separately
    - Comparator: written separately

#### Storage and Handling Precautions

1. Store out of reach of children.
2. Storing in an alternative container may cause accidents or compromise the quality of the product. This should therefore be avoided.

## Distribution of the Investigational Product

The investigator is responsible for all aspects of investigational product distribution, including maintenance of the distribution records for the investigational product.

- Upon receipt of the investigational product, the investigator or investigator’s proxy must confirm receipt by signing (including initials) and dating the document provided by the sponsor or sponsor’s proxy. The document must then be returned to the investigational product supplier. A copy should be stored in the investigator’s file.
- If necessary, the recipient of the investigational product must receive and keep a log of the storage temperature during transport.
- The specifics of the investigational product distribution must be accurately recorded in the investigator or sponsor’s study drug receipt / shipment form. At the monitoring visit, the monitoring officer must be able to check the accuracy of such details.

The investigator must also keep the records detailed below:

- A document that confirms the administration of the investigational product to the subjects according to the protocol and its amendments.
- A document that confirms that there is appropriate management of the supplied investigational product and no discrepancy between shipment and receipt.
- If necessary, a document that confirms the appropriate storage of the investigational product (e.g. temperature).

Unused investigational product should not be discarded or used for purposes other than this clinical trial. Unused investigational product supplied to a subject must not be re-supplied to other subjects.

## Treatment compliance

The number of investigational products administered during the study will be recorded, and this number will be used to evaluate treatment compliance.

## Blinding

- Confirmation of the inability to differentiate between the investigational products:

This study applies double-blinding to which of the experimental drug or the comparator is being administered. The investigational products for this study (experimental drug: Naxozol tablet; comparator: Celebrex capsule) differ in color and packaging, so this study is a double-placebo study that uses a placebo for the experimental drug that is equal in form, shape, and packaging to the experimental drug, and a different placebo for the comparator that is equal in form, shape, and packaging to the comparator, ensuring that the double-blinding of the investigator and subjects will be maintained during the study period. Neither the investigator nor the subject can be aware of whether the experimental drug or the comparator was administered to the subject until the termination of the study.

- Preparation and maintenance of the randomization code and unblinding envelope:

The randomization code will be created by the sponsor or a proxy randomization code generator designated by the sponsor. The generated randomization code will be sent to the person in charge of packaging the experimental drug and comparator for [name] (Department of Orthopedics, Severance Hospital). The unblinding envelope will be provided to the investigator in case emergency unblinding is necessary. The unblinding envelope will be safely sealed with the study arms for the study subjects until the time of unblinding. After the termination of the study, a monitoring agent will confirm that the unblinding envelope remains sealed.

- Collection of the investigational product:

The blind must be maintained until the time of unblinding. For this, the investigational products must be sealed and stored appropriately.

- Unblinding of the double-blind:

Neither the investigator nor the subject should know whether the experimental drug or the comparator was administered. After the termination of the study, the sponsor will open the code to the investigator for data analysis. The randomization code should not be accessed until uncoding, according to appropriate process after the termination of study. However, unblinding for the entire subject group or for individual subjects is possible for the evaluation of safety and efficacy by the investigator.

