## Early termination of study

The study can be terminated early in the following cases (in which there is new information regarding negative effects of the investigational products on the risk / benefit ratio for the subjects):

- - Evidence of lack of efficacy.
  - New and important drug-related adverse events or an unexpectedly high incidence rate or severity of one or more previously known adverse events.
  - Other safety-related reasons.
  - An inability to medically or ethically justify continuation of the study, as per the sponsor’s assessment.
  - The rate of subject enrolment at a study site is deemed to hinder the enrolment of the required number of subjects for the study.
  - The cessation of sale or supply of the investigational products.

If this study is terminated early, a government regulatory authority or clinical study review committee will be notified according to the relevant regulations. The study can be suspended or terminated by a request from the government regulatory authority.

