## Emergency unblinding

The unblinding envelope provided to the investigator should only be opened in emergency situations. If unblinding is needed, the investigator must inform the sponsor before unblinding the subject or subjects. If the randomization is unblinded, the sponsor must be informed immediately over the phone, and the reason and date of the unblinding must be recorded in a separate document. The opened unblinding envelope must be dated and signed by the investigator.

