## 7.6. Interim analysis

Interim analysis will not be performed.

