## Appendix 2. Investigator survey

#### (Leeds Dyspepsia Questionnaire, LDQ)

| 1 | Over the last FOUR WEEKS have you had any **indigestion** (a pain in the upper abdomen) (see picture)?  YES [ ] NO [ ]  *If the answer is no please go to question 2.*  How severe has your indigestion been over the last FOUR WEEKS?  Very mild [ ] Mild [ ] Moderate [ ] Severe [ ]  Very severe [ ] | [figure not shown] |
| --- | --- | --- |
|  |  | epigastric pain, discomfort, or burning.  * Note the difference in location from #2! |
| 2 | Over the last FOUR WEEKS have you experienced heartburn (a burning feeling behind the breast bone) (see picture)?  YES [ ] NO [ ]  *If the answer is no please go to question 3.*  How severe has your heartburn been over the last FOUR WEEKS?  Very mild [ ] Mild [ ] Moderate [ ] Severe [ ]  Very severe [ ] | [figure not shown] |
|  |  | Chest burning, discomfort, or pain. |
| 3 | Over the last FOUR WEEKS has **food or drink ever stuck behind your breast bone as it went down**?  YES [ ] NO [ ]  *If the answer is no please go to question 4.*  How severe has your symptom been over the last FOUR WEEKS?  Very mild [ ] Mild [ ] Moderate [ ] Severe [ ]  Very severe [ ] | Chest discomfort or pain when swallowing, odynophagia (ddx) or dysphagia. |
| 4 | Over the last FOUR WEEKS have you experienced any **regurgitation** (an acid taste coming up into your mouth from your stomach)?  YES [ ] NO [ ]  *If the answer is no please go to question 5.*  How severe has your regurgitation been over the last FOUR WEEKS?  Very mild [ ] Mild [ ] Moderate [ ] Severe [ ]  Very severe [ ] | Reflux of gastric contents (reflux) (ddx) belching, vomiting, or rumination. |

| 5 | Over the last FOUR WEEKS have you noticed excessive **burping or belching**?  YES [ ] NO [ ]  *If the answer is no please go to question 6.*  How severe has your belching been over the last FOUR WEEKS?  Very mild [ ] Mild [ ] Moderate [ ] Severe [ ]  Very severe [ ] | Belching, oral expulsion of gas only. |
| --- | --- | --- |
| 6 | Over the last FOUR WEEKS have you experienced any **nausea** (a feeling of sickness without actually being sick)?  YES [ ] NO [ ]  *If the answer is no please go to question 7.*  How severe has your nausea been over the last FOUR WEEKS?  Very mild [ ]  Mild [ ] Moderate [ ]  Severe [ ]  Very severe [ ] | Nausea, retching. |

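### Protocol Section 5.8 ends by letting the investigator, who conducts the LDQ, unblind one subject or all of them to evaluate efficacy, against the protocol's other blinding rules

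*Protocol*

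**What the plan says.** Most of the protocol's text on blinding is strict. Section 5.8 states: "Neither the investigator nor the subject can be aware of whether the experimental drug or the comparator was administered to the subject until the termination", meaning when the trial ends. Under its heading on breaking the double-blind it has the sponsor open the code to the investigator for data analysis once the study has ended, and adds: "The randomization code should not be accessed until uncoding, according to appropriate process after the termination of study." Section 7.2 repeats that neither investigator nor subject can learn the arm before the study ends. Section 5.9 states: "The unblinding envelope provided to the investigator should only be opened in emergency situations." It also requires that the sponsor be told and that the reason and date be recorded.

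The last sentence of Section 5.8 then says: "However, unblinding for the entire subject group or for individual subjects is possible for the evaluation of safety and efficacy by the investigator."

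Three other places bear on this:
- Section 4.8 lists "Evidence of lack of efficacy" among the grounds for ending the study early, without naming the data or the rule behind it.
- Section 7.6 says: "Interim analysis will not be performed."
- The LDQ form is headed "Appendix 2. Investigator survey". In Section 6.1 the LDQ is conducted at Visits 2 and 3, whereas the GSRS and EQ-5D are handed to the subjects to answer.

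**The concern.** A site cannot follow both rules. One allows the envelope to be opened only in an emergency, with a record. The other allows any subject, or the whole trial, to be unblinded for evaluating efficacy, and asks for no reason or record.

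The permission goes to the person who conducts the primary endpoint assessment. The LDQ rests on graded symptom severity obtained in an exchange between investigator and patient. Knowledge of the arm can affect how questions are put and how answers are graded. Section 4.2 relies on double-blinding to reduce this kind of bias. In a non-inferiority trial, a bias towards the experimental drug leads directly to a false claim of non-inferiority.

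Section 4.8 adds a smaller ambiguity. It allows a stop for lack of efficacy without saying that unblinded comparative data from this trial are excluded as the evidence, although Section 7.6 rules out an interim analysis.

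**Working it through.** **1. The passages side by side**

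| Place | Who may learn the allocation | When |
|---|---|---|
| 5.8, earlier text | Nobody at the site; the sponsor then opens the code | After the study ends |
| 5.9 | Investigator, via the envelope | Emergencies only, sponsor informed, reason and date recorded |
| 7.2 | Neither investigator nor subject | Not before the study ends |
| 5.8, last sentence | Investigator, for one subject or all | No limit stated; purpose is safety and efficacy evaluation |

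The last row cannot be reconciled with the other three unless it is confined to the time after the study.

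**2. The plan's own sample size**

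Inputs from Section 7.1: SD 0.65, margin 0.40, one-sided alpha 0.025, power 80%, drop-out 20%.

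n per arm = 2 × 0.65² × (1.96 + 0.842)² / 0.40² = 41.46, rounded up to 42. Enrolled: 42 / 0.80 = 52.5, rounded up to 53. Both match the protocol.

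SE of the difference = 0.65 × √(2/42) = 0.142. Power at a true difference of zero = Φ(0.40/0.142 − 1.96) = 80.5%.

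**3. Illustration of assessor bias**

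Assume that the true difference equals the margin and that knowledge of the arm moves the estimated difference by b in Naxozol's favour, net over the whole trial. The values of b are assumptions. The chance of falsely concluding non-inferiority is Φ(b/0.142 − 1.96).

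| b (LDQ points) | Share of margin | False non-inferiority |
|---|---|---|
| 0 | 0 | Φ(−1.96) = 2.5% |
| 0.05 | one eighth | Φ(0.35 − 1.96) = about 5% |
| 0.10 | one quarter | Φ(0.70 − 1.96) = about 10% |

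**4. What a stop for lack of efficacy would do**

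Assume one unblinded look at half the information that can only stop the trial, when the observed difference (Naxozol minus celecoxib) exceeds a threshold. The protocol states neither the timing nor the threshold. With Z = (0.40 − difference)/SE and a correlation of √0.5 between the look and the final test, a claim requires passing the look and then Z > 1.96 at the end.

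| Stop if the difference exceeds | One-sided type I error | Power |
|---|---|---|
| No look | 2.5% | 80.5% |
| 0.40 | 2.47% | 80.2% |
| 0.20 | 2.0% | 74.2% |
| 0 | 0.8% | 48.1% |

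Type I error does not rise in any row. Power falls, by an amount that depends on the unstated rule.

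**The case against.** The best defence is that the sentence describes decoding after the study. It follows text on the sponsor opening the code for data analysis, and it gives no timing of its own. This is possible but weak. The same paragraph already covers opening the code after the study, so the sentence would add nothing. Its opening word marks an exception to the ban stated just before it. Unblinding individual subjects also has little purpose once the whole code is open.

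A second defence is that the blind has real safeguards: matching placebos for both drugs, a sealed envelope, a monitor's check of the seal, notice to the sponsor, and a dated record. This stands. The blind is not unprotected; one sentence contradicts what protects it.

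Third, every LDQ item asks what the patient felt, and opening the code to the investigator does not unblind the patient. This also stands in part: the bias is possible, not certain, and its size is unknown.

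Stronger readings are tempting but not supported:
- A reader might infer that an unblinded look inflates the type I error. That would need an early declaration of success. Section 7.5.2 provides one final test against 0.40, and the only efficacy-related stop in Section 4.8 is for lack of efficacy.
- A reader might infer that lack of efficacy could be learned only by unblinding this trial. Section 4.8 introduces its list with new information on risk and benefit, which could come from outside; Naxozol has been in use since 2013.
- A reader might count the absence of a data monitoring committee, or a code generated by the sponsor, as an error. Neither contradicts anything in the protocol, and Section 5.8 already allows a proxy to generate the code.

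**Conclusion.** The last sentence of Section 5.8 is wrong as written. It permits unblinding for efficacy evaluation by the person who conducts the primary endpoint assessment, without limit in time or number of subjects, and it conflicts with the rest of Section 5.8 and with Sections 5.9 and 7.2.

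The harm is possible assessor bias if the permission is used before the last Visit 3. The figures of about 5% and 10% against a nominal 2.5% show how sensitive the test is; they do not predict what would happen. They rest on the assumed net shifts of 0.05 and 0.10, on the protocol's SD of 0.65, and on 42 evaluable subjects per arm.

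The silence in Section 4.8 is secondary. If filled by an unblinded look at the trial's own data, it would threaten power, with the loss ranging from negligible to severe under the thresholds tried.

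**What to change.** 1. Delete the last sentence of Section 5.8, or limit it to the time after database lock.
2. State in Section 5.8 that before database lock the only unblinding allowed is emergency unblinding under Section 5.9.
3. State in Section 4.8 that the lack-of-efficacy ground will not rest on unblinded comparative data from this trial, in line with Section 7.6. The ground itself need not be removed.

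The cost is a wording amendment. Sample size, visits and analysis stay as they are.
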